## **1. Study objective**

To evaluate the efficacy and safety of Qing-Xin-Jie-Yu Granules (QXJYG) for intermediate coronary lesions (ICL) in patients with stable coronary artery disease (SCAD).

## **2. Participants**

### **2.1 Diagnostic criteria**

- 1) Diagnosis criteria of ICL: 2021 ACC/AHA/SCAI Guideline for Coronary Artery Revascularization.
- 2) Diagnosis criteria of SCAD: 2014 ACC/AHA/AATS/PCNA/SCAI/STS focused update of the guideline for the diagnosis and management of patients with stable ischemic heart disease; 2021 AHA/ACC/ASE/CHEST/SAEM/SCCT/SCMR Guideline for the Evaluation and Diagnosis of Chest Pain.

### **2.2 Inclusion criteria**

- 1) Patients with SCAD who have at least one major coronary artery with luminal diameter stenosis of 50% to 70% confirmed by coronary computed tomography angiography (CCTA).
- 2) Heart function grade NYHA grade I - II.
- 3) Patients aged 18 to 75 years.
- 4) Patients who are informed and voluntarily sign the ICF.

### **2.3 Exclusion criteria**

- 1) Patients have previously undergone coronary stent implantation, coronary artery bypass grafting or MI within three months.
- 2) Lesions with diameter stenosis  $\geq 50\%$  in the left main coronary artery or in all three major arteries.
- 3) Diffuse lesions throughout the diseased vessels.
- 4) Severe blood pressure fluctuations or difficult-to-control hypertension with systolic blood pressure  $\geq 160\text{mmHg}$  and diastolic blood pressure  $\geq 100\text{mmHg}$  in the past 3 months.
- 5) Resting heart rate  $> 100$  beats/min and difficult to control.
- 6) Patients have previously undergone other cardiac operations, such as valve replacement.
- 7) Patients with severe cardiac, hepatic or renal insufficiency that are unsuitable for CCTA and related examination and treatment.
- 8) Patients suffering from mental disorders.
- 9) Patients suffering from hepatitis, tuberculosis, AIDS, or other infectious diseases.
- 10) Allergic sufferers.
- 11) Pregnant and lactating women
- 12) Life expectancy is less than one year.
- 13) Participation in other clinical trials within the last three months.

### **2.4 Elimination criteria**

- 1) Cases where the patient selection violates the inclusion/exclusion criteria and should not have been randomized.
- 2) Subjects who do not cooperate with randomization or do not take any investigational drugs after randomization, or use drugs very minimally (<10%).
- 3) Cases where prohibited drugs were used, making it impossible to assess efficacy and safety.
- 4) No data available after randomization.

The decision to exclude such cases must be made during the blind review by the principal investigator, data manager, statistical analysis expert, and sponsor after discussion.

## ***2.5 Withdrawal criteria***

- 1) Conditions continue to worsen.
- 2) Comorbidities, complications, or special physiological changes.
- 3) Poor compliance or use of prohibited drugs.
- 4) Adverse events or serious adverse events.
- 5) Leak of blindness

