### **2.5.1 Determination of dropout cases**

Subjects who have completed the informed consent form (ICF) and qualified for entry into the trial but withdraw for any reason before completing the specified observation period, are considered as dropout cases. The reasons for dropout should be documented. If baseline efficacy data are available, the last recorded primary efficacy results should be used as the final result for statistical analysis, and the case report forms (CRFs) should be retained for reference.

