### **2.5.2 Handling of dropout cases**

After a subject drops out, the investigator should maintain contact with the subject, inquire about the reasons for dropout, record the last medication administration time, and make the dropouts complete as many assessment items as possible. Then the CRF should be completed. If someone withdraws due to allergic reactions, adverse events, or ineffective treatment, the investigator should provide appropriate treatment measures and some form of financial compensation to ensure the subject's rights.

All enrolled cases, regardless of dropout status, should have their data recorded and retained in the CRF. These records are essential for the Full Analysis Set (FAS) analysis. Dropout cases do not need to be supplemented separately.

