## **6. Follow-up**

The treatment period will last for 6 months, and the follow-up will be a total of 12 months, with visits scheduled at the following time points: before treatment (visit 1),

2 months after treatment (visit 2), 4 months after treatment (visit 3), 6 months after treatment (visit 4), and 12 months after treatment (visit 5).

The process of discontinued case exiting the trial:

- a) Retrieve and record remaining drugs and packaging.
- b) Inquire about any adverse events or other relevant information.
- c) Perform a physical examination.
- d) Complete efficacy and safety evaluation.
- e) Record the reason for discontinuation.

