  - Estimation: The least squares method will be used to estimate the mean difference between groups and the 95% CI.
- c) Serum inflammatory factors, blood lipids, and carotid ultrasound indicators
- Description: Values at baseline and 6 months after treatment, as well as the difference from baseline to 6-month will be described.
  - Intergroup Comparisons: A linear mixed model will be used, with the dependent variable being the difference from baseline to 6-month. Fixed effects include group and center, and random effects include the subjects, with baseline values as covariates.

- Estimation: The least squares method will be used to estimate the mean difference and 95% CI.
- 3) Endpoint Event: MACE
- Description: The incidence rate of MACE from baseline to the 1-year follow-up will be described.
  - Intergroup Comparisons: The Cox proportional hazards model will be used, with the dependent variable being the occurrence of MACE and the survival time variable being the time from baseline to either the occurrence of MACE or the end of follow-up. The primary independent variable is the group. Covariates include age, gender, BMI, systolic blood pressure, diastolic blood pressure, LDL-C, FBG, smoking status, alcohol consumption, family history of early-onset cardiovascular disease, presence of cerebrovascular disease, peripheral vascular disease, diabetes mellitus, hypertension, dyslipidemia, concomitant use of PCSK-9 inhibitors, and study center.
  - Estimation: The partial likelihood method will be used to estimate the hazard ratio and its 95% CI.
- 4) Subgroup analyses: Considering the significant impact of concomitant diabetes and the use of PCSK-9 inhibitors on drug efficacy, subgroup analysis of the primary efficacy outcome and endpoint events will be performed in SCAD patients with diabetes and SCAD patients with the use of PCSK-9.

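### Stopping study drug is not separated from leaving the study, so month-6 CT-FFR and later MACE can be lost for outcome-related reasons

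*Protocol*

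**What the plan says.** Section 2.5 gives a single list of withdrawal criteria. Three of its five items are "Conditions continue to worsen", "Adverse events or serious adverse events" and "Leak of blindness". The list does not say whether meeting a criterion ends study drug, study participation or both.

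Section 2.5.1 says that consented, eligible subjects who "withdraw for any reason before completing the specified observation period, are considered as dropout cases". Where baseline efficacy data exist for them, "the last recorded primary efficacy results should be used as the final result for statistical analysis". Section 6 sets out steps under the line "The process of discontinued case exiting the trial"; they include an efficacy and safety evaluation but no later visit.

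Other text softens this. Section 2.5.2 tells the investigator to stay in contact after dropout and to "make the dropouts complete as many assessment items as possible", and keeps the records of dropouts for the FAS. Section 3.5.2 wants the data of unblinded patients kept complete.

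The flow chart in section 12 schedules CT-FFR at baseline and month 6 only, and MACE is the only assessment at month 12. Section 9.2.2 analyses the baseline-to-month-6 change in CT-FFR. For MACE it uses a Cox model with survival time defined as "the time from baseline to either the occurrence of MACE or the end of follow-up". Section 9.2.1 says missing efficacy data in the FAS are multiply imputed.

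**The concern.** Worsening and adverse events are related to the outcomes this trial measures. If patients who meet these criteria leave the trial, those missing at month 6 and month 12 are not a random subset.

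Loss of blinding is linked to outcome less directly. Section 3.5.2 allows emergency unblinding for severe adverse events, severe complications or deteriorating symptoms, and section 2.5 does not say whether such unblinding falls under its fifth criterion.

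Two results are at stake. The primary CT-FFR comparison would rest on substituted or imputed values in patients who may have done worst. The MACE hazard ratio would depend on censoring that may be informative. An analysis plan cannot repair either, because it cannot recover visits that were never held.

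**Working it through.** The documents give no withdrawal rate by reason or by arm and no MACE rate. The only related figure is the 10% dropout allowance in section 3.4, which is 0.10 × 120 = 12 patients for dropout of every kind. The sizes below are therefore illustrations under stated assumptions.

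**1. What is required after withdrawal**

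| Protocol section | Asked for | Month-6 CT-FFR required? | Month-12 MACE contact required? |
|---|---|---|---|
| 2.5.2 | Contact; assessments as far as possible | No | No |
| 3.5.2 | Complete data if unblinded | Not named | Not named |
| 6 | Evaluation at exit | No | No |

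**2. What value enters the CT-FFR analysis**

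CT-FFR is scheduled only at baseline and month 6. Under section 2.5.1, a dropout without an exit scan has the baseline value as last value, so the change is baseline − baseline = 0. A dropout with an exit scan, say at month 2, has that off-schedule value treated as final. Under section 9.2.1 the same missing value would be multiply imputed instead. The two rules differ and the protocol does not say which governs.

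**3. Size for CT-FFR**

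Let f be the fraction withdrawn in an arm and g their true decline, scored as 0. Each arm mean is then too high by f × g, so the error in the difference (drug − placebo) is (fT − fC) × g.

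- Assumed fT = 5%, fC = 15%, g = 0.05: (0.05 − 0.15) × 0.05 = −0.005
- Same fractions, g = 0.10: −0.010
- Fractions reversed: +0.005 to +0.010
- Equal fractions and equal g: 0

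Against the section 3.4 margin of 0.03, this is 0.005/0.03 = 17% to 0.010/0.03 = 33%. Against the assumed difference of 0.92 − 0.77 = 0.15, it is 3% to 7%. If g is read instead as the withdrawn patients' shortfall relative to completers, the same formula gives the error of a completers-only comparison.

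**4. Size for MACE**

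Assume 12-month MACE of 10% on placebo and 5% on drug, with 60 per arm: 6 v 3 events, a true ratio of 3/6 = 0.50. The ratio of counts stands in for the hazard ratio. Now assume that some events fall after withdrawal and are not ascertained.

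| Placebo events lost | Drug events lost | Observed, placebo v drug | Ratio |
|---|---|---|---|
| 50% | 25% | 3 v 2.25 | 0.75 |
| 25% | 50% | 4.5 v 1.5 | 0.33 |
| Equal | Equal | proportional | 0.50 |

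Events before or at withdrawal are counted in every row.

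**The case against.** The strongest reply is that the protocol does not abandon these patients. Contact continues, as much assessment as possible is sought, an efficacy evaluation is made at exit, and unblinded patients' data are to be complete. A site that follows section 2.5.2 diligently may obtain both outcomes. This stands to the extent that loss is a risk and not a stated consequence. It does not close the gap, because an effort clause is weaker than a scheduled visit and section 6 describes the patient as exiting.

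Several stronger readings are tempting, and the documents do not support them:

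- *That month-6 and month-12 data are lost for every withdrawn patient.* Sections 2.5.2, 3.5.2 and 6 point the other way.
- *That the Cox model censors at withdrawal by rule.* Section 9.2.2 refers only to the end of follow-up. Censoring at exit follows only if contact ceases, and a MACE that occurs before exit is counted.
- *That emergency unblinding automatically triggers withdrawal.* Section 2.5 neither says so nor exempts it. Section 3.5.2 also says that patients who withdrew for efficacy reasons are not to be unblinded.
- *That the bias favours the drug.* It can go either way or vanish.

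The effect may also be small beside sampling error. With 6 v 3 events in 60 per arm, the standard error of the log ratio is √(1/3 − 1/60 + 1/6 − 1/60) = 0.683, giving a 95% interval of about 0.13 to 1.9. A shift from 0.50 to 0.75 lies well inside it, and MACE is not the primary outcome. This is fair and limits the weight of the point, but imprecision does not excuse avoidable bias.

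**Conclusion.** The concern holds as a design weakness that should be corrected. The protocol merges stopping drug with leaving the study, uses outcome-related grounds for withdrawal, and requires neither the month-6 CT-FFR nor the month-12 MACE contact afterwards. Month-6 CT-FFR and post-withdrawal MACE can therefore be lost in an outcome-related way, and sections 2.5.1 and 9.2.1 disagree on how a missing primary value is handled.

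Size and direction are unknown. The CT-FFR range rests on assumed 5% v 15% withdrawal and an assumed decline of 0.05 to 0.10; the MACE range rests on assumed event rates and loss fractions. Both biases disappear under equal loss (for CT-FFR, with equal decline as well). Whether and when study drug should be stopped is not judged here.

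**What to change.** In sections 2.5, 2.5.1, 2.5.2 and 6, state that meeting a withdrawal criterion does not by itself end study follow-up. Randomised patients should keep the scheduled month-6 CT-FFR/CCTA, where the investigator considers the scan suitable, and the month-12 MACE contact, unless they withdraw consent for follow-up. The suitability exception is needed because section 2.5 includes withdrawal for comorbidities and complications, and section 2.3 recognises patients for whom CCTA is unsuitable.

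For values still missing, reconcile the carry-forward rule in section 2.5.1 with the multiple imputation in section 9.2.1, so that one rule governs the primary analysis.

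The cost is protocol wording plus, at the planned allowance, up to about 12 scans and contacts already in the schedule. One small downside is that some off-drug or post-revascularization CT-FFR values will enter the comparison, and the latter may reflect the procedure more than the drug.

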### **2.5.1 Determination of dropout cases**

Subjects who have completed the informed consent form (ICF) and qualified for entry into the trial but withdraw for any reason before completing the specified observation period, are considered as dropout cases. The reasons for dropout should be documented. If baseline efficacy data are available, the last recorded primary efficacy results should be used as the final result for statistical analysis, and the case report forms (CRFs) should be retained for reference.

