### ***9.1 Population for Statistical Analysis***

- 1) Intent-to-Treat (ITT) Analysis: All participants who express the intention to receive treatment and sign the informed consent form will be included in the analysis.
- 2) Full Analysis Set (FAS): This includes participants who signed the informed consent form, received the investigational drug at least once, and have corresponding efficacy indicator records. Baseline data analysis will focus on the FAS as the target population, and efficacy analysis will be based primarily on FAS results.
- 3) Per-Protocol Set (PPS): This includes participants who meet the inclusion criteria, do not meet the exclusion criteria, and complete the treatment regimen. PP analysis involves analyzing participants who adhere well to the trial protocol.
- 4) Safety Set (SS): This includes participants with safety indicator records. Missing values for safety indicators will not be estimated.

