### ***9.2 Statistical Analysis method***

#### 9.2.1 General Considerations

- 1) All statistical tests will be two-sided, with a P-value  $\geq 0.05$  considered statistically significant.
- 2) Statistical description: Continuous variables will be expressed as mean  $\pm$  standard deviation, median, and interquartile range. Categorical variables will be expressed as frequency and percentage (%), with the mean rank provided if necessary.
- 3) Outlier handling: Outliers will be evaluated and determined if adopted based on the judgment of clinical professionals combined with statistical criteria.
- 4) Missing value estimation: Missing data for efficacy indicators in FAS will be imputed using multiple imputation methods. Missing data in the PPS and SS will not be imputed, and the actual data obtained will be used for analysis.

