#### 9.2.2 Efficacy Analysis

- 1) Primary Efficacy Outcome: CT-FFR.
  - Description: CT-FFR values of the target vessels at baseline and 6 months after

treatment, as well as the difference from baseline to 6-month will be described. For multiple vessel lesions, the CT-FFR value of the most severely narrowed vessel will be selected.

- Intergroup Comparison: A linear mixed model will be used for comparison between groups. The dependent variable is the difference in CT-FFR from baseline to 6-month. Fixed effects include group and center, while random effects include subjects. Covariates include baseline values of CT-FFR, age, gender, BMI, systolic blood pressure, diastolic blood pressure, LDL-C, FBG, smoking status, alcohol consumption, family history of early-onset cardiovascular disease, presence of cerebrovascular disease, peripheral vascular disease, diabetes mellitus, hypertension, dyslipidemia, and concomitant use of PCSK-9 inhibitors.
  - Estimation: The least squares method will be used to estimate mean differences and 95% confidence intervals (CI).
- 2) Secondary Efficacy Outcomes
- a) Coronary imaging assessment indicators
- Description: %DS measurement will use the most narrowed location as the result; CACS and Gensini scores will use the total score as the result. Values of %DS, CACS, and Gensini scores at baseline and 6 months after treatment, as well as the difference from baseline to 6-month will be described.
  - Intergroup Comparison. A linear mixed model will be used, with the dependent variable being the difference from baseline to 6-month. Fixed effects include group and center, random effects include subjects, and covariates include baseline values.
  - Estimation: The least squares method will be used to estimate the mean difference and 95% CI.
- b) SAQ score
- Description: SAQ scores at baseline, 2, 4, and 6 months after treatment will be described, along with the differences from baseline to 2, 4, and 6 months.
  - Intergroup Comparisons: A mixed model for repeated measures will be used, with the dependent variable being the difference in SAQ scores at 2, 4, and 6 months relative to baseline, with the primary assessment time point at 6 months after treatment. Fixed effects include group and center, random effects include subjects. Covariates include baseline SAQ scores, visit times, the interactions between baseline and visit, and the interactions between treatment group and visit.

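### Sections 2.5.1 and 9.2.1 give two incompatible, unranked rules for a dropout's missing month-6 CT-FFR in the primary analysis: last recorded value and multiple imputation.

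*Protocol*

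**What the plan says.** Section 2.5.1 deals with participants who leave before the end of observation. Provided that baseline efficacy data exist, "the last recorded primary efficacy results should be used as the final result for statistical analysis".

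Section 9.2.1, item 4, gives another rule: "Missing data for efficacy indicators in FAS will be imputed using multiple imputation methods". Section 9.1 names the population to which this applies as the primary one: "efficacy analysis will be based primarily on FAS results".

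FAS membership under section 9.1 requires that participants signed consent, "received the investigational drug at least once, and have corresponding efficacy indicator records". It does not say whether a baseline record is enough. Section 2.5.2 says of the records of all enrolled cases, dropouts included: "These records are essential for the Full Analysis Set (FAS) analysis".

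For the primary model in section 9.2.2, "The dependent variable is the difference in CT-FFR from baseline to 6-month". The flow chart in section 12 schedules CT-FFR at baseline and month 6 and at no other visit. Sections 2.5.2 and 6 ask for assessments, including an efficacy evaluation, when a participant leaves, but neither names CT-FFR.

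**The concern.** The two rules apply to the same missing value in the same population, and no sentence gives one of them priority. An analyst can follow the protocol and report either result.

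They are not close substitutes. The only condition on the last-value rule is that a baseline value exists, so it expressly reaches participants who have nothing else. For them the last CT-FFR is the baseline CT-FFR, and the analysed change is exactly 0, entered as if it had been observed. Section 2.5 lists worsening and adverse events among the reasons for withdrawal, so an unchanged CT-FFR is a doubtful assumption for these participants. Multiple imputation draws the missing change from a model and carries its uncertainty into the standard error.

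At stake are the primary estimate and its confidence interval. The unclear FAS condition adds to this: read as requiring a post-baseline CT-FFR, it would remove the participants for whom the imputation is meant.

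**Working it through.** The plan gives no figure for the effect of its missing-data rules, so there is none to reproduce. Its sample size formula does not enter this check.

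**Inputs from section 3.4.** Means of 0.92 and 0.77, so a planned difference of 0.92 − 0.77 = 0.15; SD 0.13; 120 patients at 1:1, so 60 per arm; maximum dropout 10%.

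**Assumptions.** The SD of 0.13 is stated for post-treatment values; I use it for the change, for which no SD is given. Mean change in completers is m_T = 0.15 (treated) and m_C = 0 (control). All dropouts leave before month 6 without an exit scan. The comparison is unadjusted; covariate adjustment would alter the standard errors.

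**Difference under each rule.** With dropout shares d_T and d_C:

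- Last value (change = 0 in dropouts): (1 − d_T)·m_T − (1 − d_C)·m_C
- Imputation under missing at random without auxiliary information, or completers only: m_T − m_C

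At 10% per arm: 0.9 × 0.15 − 0.9 × 0 = 0.135, against 0.150.

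**Standard error under each rule.** With the zeros included, each arm's variance is (1 − d)(0.13² + m²) − [(1 − d)m]².

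- Treated: 0.9 × (0.0169 + 0.0225) − 0.135² = 0.017235
- Control: 0.9 × 0.0169 = 0.01521
- Last value: √[(0.017235 + 0.01521)/60] = 0.0233
- Completers, 54 per arm: 0.13 × √(2/54) = 0.0250

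The last-value standard error is about 7% smaller (0.0233/0.0250 = 0.93), although no information has been added. The 95% intervals are 0.135 ± 0.046 and 0.150 ± 0.049.

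**Other dropout patterns, same assumptions.**

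| Dropout, treated / control | Last value: difference (SE) | Missing at random or completers: difference (SE) |
|---|---|---|
| 0% / 0% | 0.1500 (0.0237) | 0.150 (0.0237) |
| 10% / 10% | 0.1350 (0.0233) | 0.150 (0.0250) |
| 20% / 20% | 0.1200 (0.0226) | 0.150 (0.0265) |
| 15% / 5% | 0.1275 (0.0236) | 0.150 (0.0251) |
| 5% / 15% | 0.1425 (0.0229) | 0.150 (0.0251) |

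**Direction of bias.** The table might suggest that the last-value rule only dilutes. It does not. Suppose the drug has no effect and every patient's CT-FFR changes by −0.05 (an assumed figure).

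- 15% treated and 5% control dropout: 0.85 × (−0.05) − 0.95 × (−0.05) = +0.005, which favours the drug
- 5% and 15%: −0.005
- 10% and 10%: 0

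**The case against.** **The effect at planned dropout is modest.** This stands. Under the planning assumptions the estimate is 5.8 standard errors from zero with the last value (0.135/0.0233) and 6.0 without (0.150/0.0250). The choice would rarely decide the trial on those assumptions. It matters more if the true effect is smaller or dropout is higher or unequal.

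**The last value need not be the baseline.** A reader might infer that carrying forward always means no change. The documents do not support that. Sections 2.5.2 and 6 ask for assessments at exit, so a post-baseline scan may exist, and a participant who leaves after month 6 already has the month-6 value. But CT-FFR is not named among the exit assessments, and an exit scan taken earlier is still not the month-6 value that the model uses.

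**Section 9.1 is not a third rule.** A reader might infer that the FAS condition excludes dropouts and makes the primary analysis a complete-case one. That is one reading only. Section 2.5.2 treats dropouts' records as needed for the FAS, and section 9.2.1 expects FAS members with missing efficacy data. The wording is ambiguous, no more.

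**The eliminations in section 2.4 are another matter.** Items such as "Cases where prohibited drugs were used, making it impossible to assess efficacy and safety" and "No data available after randomization" might be read as a further rule for missing CT-FFR. Those exclusions are decided case by case at blind review and concern analysis sets.

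**Multiple imputation does not cure informative dropout.** This also stands. Take assumed changes of +0.09 in treated completers, 0 in control completers and −0.08 in all dropouts. With 15% treated and 5% control dropout the true difference is 0.85 × 0.09 − 0.15 × 0.08 + 0.05 × 0.08 = 0.0685. The last-value rule gives 0.85 × 0.09 = 0.0765 and missing-at-random imputation gives 0.09, which is further off. With the dropout rates swapped, the truth is 0.95 × 0.09 − 0.05 × 0.08 + 0.15 × 0.08 = 0.0935, the last value gives 0.0855, and imputation, again at 0.09, is closer. Such examples do not show that imputation is always nearer the truth. They show that a sensitivity analysis is needed.

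**The analysis plan could settle it.** It may, since section 3.5.3 has it finalised before database lock. The protocol would still state both rules.

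**Conclusion.** The contradiction between sections 2.5.1 and 9.2.1 is real and governs the primary estimate. With 10% dropout per arm, no exit scans and an SD of change of 0.13, the choice of sentence moves the planned difference between 0.150 and 0.135 and the standard error between 0.0250 and about 0.0233. With unequal dropout the last-value rule can bias in either direction, including in favour of the drug when there is no effect. The FAS wording in section 9.1 is a secondary ambiguity that could be read to remove the participants to be imputed. The contradiction does not depend on the numerical assumptions; its size does.

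**What to change.** - **Section 2.5.1:** delete the last-value sentence, or relegate it explicitly to a sensitivity analysis.
- **Section 9.2.1:** keep multiple imputation and state that it is the single primary method for missing month-6 CT-FFR in the FAS.
- **Section 9.1:** state that a post-baseline CT-FFR record is not required for FAS membership.
- **Sensitivity analysis:** because withdrawal can follow worsening, add one for informative dropout, for example delta-adjusted imputation, in which the imputed changes of dropouts are shifted over a prespecified range in each arm.

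These changes should be made before the first unblinding, so that the rule cannot depend on the result. They need no new data. The cost is a slightly wider confidence interval than under carried-forward values (half-width about 0.049 against 0.046 in the planned case) and a little more analysis work.
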